### Safety aspects

#### Specification of safety variables

##### Training for surgeons

In each operation there will be a surgeon (senior surgeon) who has experience of at least 100 pp-Whipple procedures. The operation will be carried out as a standard procedure; the LigaSure™ device has been used in the department for several years already.

##### Concomitant medication

Concomitant medication will not be recorded because the primary operating time of the two dissection techniques is a local and technical endpoint. Therefore, a systemic pharmacological interaction with the medication of the patient will be very unlikely.

##### Past medical history

Prior and concomitant illness of the patients will be documented in the CRF. The category of the primary disease (reason for pp-Whipple procedure) is one of the variables to be analyzed for baseline comparability.

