### Eligibility

#### Inclusion criteria

• Clinical suspicion of a cancerous tumour on the head of the pancreas, relied on imaging and laboratory values

• Aged 18 years or older

• Patients scheduled for primary pp-Whipple procedure

• Informed consent

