### Randomization and procedures for minimizing bias

#### Minimizing systemic bias

To achieve comparable groups for known and unknown risk factors randomization will be performed as unstratified block randomization with random block sizes in a 1:1 allocation ratio. Allocation to treatment group will be carried out by the randomization software RITA^® ^[17]. Randomization numbers that become vacant by withdrawal will be reused.

102 patients will be recruited according to the sample size calculation. Randomization will be performed independently by a study nurse of the Clinical Study Center Surgery (KSC) to the conventional group or to the LVSS group. Randomization will be carried out after patient has signed the informed consent and will be documented in the case report file of every patient. Intervention will be scheduled 1-3 days after inclusion depending on the earliest operation appointment possible.

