## Analysis

Comparisons will be made of the primary endpoints of both intervention groups for all randomized patients who underwent surgery involving the pp-Whipple procedure. Patients will be analysed as randomized applying the ITT principle [18]. In addition, a per-protocol analysis will be performed, including patients who are strictly treated according to the study protocol.

The outcome measures of the primary endpoint will be tested confirmatory applying an analysis of covariance with treatment as factor and age and BMI as continuous covariates.

Secondary endpoints will be analysed in a descriptive manner. Graphically methods will be used by means of box- and scatter- plots. For all continuous secondary endpoints a t-test will be applied, possible differences of categorical secondary endpoints will be analysed using chi-square tests. All p-values will be used as descriptive statistics only without any confirmatory value.

The secondary endpoint Quality of Life (EORTC QLQ-C30, EORTC QLQ PAN26) will be anlysed by an application of analysis of covariance that adjusts for age and EORTC QLQ-C30, EORTC QLQ PAN26 before surgery.

The following procedure will be applied for missing data:

If at least half of the items from the scale have been answered, the missing items are replaced by the average of those items that are not missing (calculated average rounded to the nearest integer). If less than half of the items from the scale have been answered, the scale is set to missing [19].

If it is evident that missing items or missing scales are related to a worsening in physical functioning, the missing values are replaced by the worst value measured in the respective intervention group at the respective time point.

The average EORTC QLQ-C30, EORTC QLQ PAN26 score can be calculated, if at least one measurement at day 30 (±10days), 90 (±10 days), 180 (±10 days), 1 year (± 1 month), 1,5 years (± 1 month), 2 years (± 1 month), 2,5 years (± 1 month) or 3 years (± 1 month) after surgery is available; if no measurement of the EORTC QLQ-C30 or EORTC QLQ PAN26 after surgery is available, the secondary endpoint is missing and the patient is therefore not included into the analysis.

All statistical analyses will be performed using SAS^® ^software, Version 9.1 (or higher) of the SAS System for Unix (SAS Institute Inc., Cary, NC, USA).

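### The recorded primary-disease category is left out of the 3-year quality-of-life, mortality and recurrence analyses, which costs precision and interpretability but does not bias them

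*Protocol article*

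**What the plan says.** All places are in the protocol article.

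- **Role of the disease category** (Safety aspects, Past medical history): "The category of the primary disease (reason for pp-Whipple procedure) is one of the variables to be analyzed for baseline comparability". No other use is stated.
- **Entry** (Inclusion criteria): "Clinical suspicion of a cancerous tumour on the head of the pancreas, relied on imaging and laboratory values". Confirmed histology is not required.
- **Allocation** (Minimizing systemic bias): "unstratified block randomization with random block sizes in a 1:1 allocation ratio".
- **Quality of life** (Analysis): "analysis of covariance that adjusts for age and EORTC QLQ-C30, EORTC QLQ PAN26 before surgery".
- **Categorical secondary endpoints** (Analysis): "possible differences of categorical secondary endpoints will be analysed using chi-square tests". By their Table 2 definitions, all-cause death up to year 3 and imaging-based local recurrence would fall here.
- **Status of these results** (Analysis): "All p-values will be used as descriptive statistics only without any confirmatory value".
- **Primary endpoint, for comparison** (Analysis): "analysis of covariance with treatment as factor and age and BMI as continuous covariates".

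**The concern.** Patients enter on suspicion, the Background says the operation is also done for inflammation and stenosis, and the protocol itself plans to tabulate disease categories. It therefore expects more than one. It is reasonable, though not documented here, to expect the underlying disease to be strongly prognostic for survival, recurrence and quality of life over 3 years.

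A baseline comparability table shows an imbalance but does nothing about it. If the arms differ visibly in disease mix, the team can report a crude 3-year difference that it has reason to doubt, or adjust after seeing the data. A model named beforehand avoids that choice and uses information already collected. The plan accepts this logic elsewhere: it prespecifies age and BMI for operating time, and age and baseline score for quality of life.

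At stake is how precisely, and how readably, the trial describes its long-term safety and oncological results. The primary endpoint is not at stake.

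**Working it through.** **The plan's own figures.** The article gives no figure on this point. Its sample size is for operating time and does not depend on it. That figure reproduces: two-sided t-test, difference 40 min, SD 66 min, alpha 5% gives 79.3% power at 43 per group and 80.3% at 44. The check below takes only the 51 per arm from it.

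**Assumed inputs.** The documents give neither the disease mix nor outcomes by disease. Let *q* be the share in a better-prognosis category (10-40%) and *g* the gap in 3-year mortality between categories (40-60 points).

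**Step 1: chance imbalance in disease mix.** SD of the arm difference in share = √(2q(1−q)/51). For q = 0.2, √(0.32/51) = 7.9 points; for q = 0.4, √(0.48/51) = 9.7 points. The 95% range is ±1.96 × SD, and the part of the mortality difference due to disease mix is that range times *g*.

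| Share q | SD of imbalance (points) | 95% range (points) | Chance of ≥10 points | Mortality part, g = 40 | Mortality part, g = 60 |
|---|---|---|---|---|---|
| 10% | 5.9 | ±11.6 | 7% | ±4.7 | ±7.0 |
| 20% | 7.9 | ±15.5 | 17% | ±6.2 | ±9.3 |
| 30% | 9.1 | ±17.8 | 23% | ±7.1 | ±10.7 |
| 40% | 9.7 | ±19.0 | 27% | ±7.6 | ±11.4 |

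**Step 2: is this on top of the standard error or inside it?** Take q = 0.2 with mortality 70% against 10%.
- Overall mortality: 0.8 × 0.70 + 0.2 × 0.10 = 0.58.
- Total variance: 0.58 × 0.42 = 0.2436. Crude standard error: √(2 × 0.2436/51) = 9.8 points.
- Variance between categories: 0.2 × 0.8 × 0.60² = 0.0576, or 23.6% of the total.
- Remaining variance: 0.2436 − 0.0576 = 0.1860. Adjusted standard error: √(2 × 0.1860/51) = 8.5 points.

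The disease-mix part has SD 0.60 × 7.9 = 4.75 points, and √(8.54² + 4.75²) = 9.8. The imbalance is therefore already a component of the crude standard error. The gain corresponds to 0.2436/0.1860 = 1.31, about 31% more patients for that endpoint.

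**Step 3: other assumed scenarios, 51 per arm.**

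| Share q | Mortality by category | Crude SE | Adjusted SE | Variance removed |
|---|---|---|---|---|
| 10% | 60% vs 20% | 9.8 | 9.5 | 6% |
| 10% | 70% vs 10% | 9.5 | 8.8 | 14% |
| 20% | 60% vs 20% | 9.9 | 9.4 | 10% |
| 30% | 70% vs 10% | 9.9 | 8.3 | 30% |
| 30% | 80% vs 10% | 9.7 | 7.4 | 43% |

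**Step 4: validity of the plain chi-square test.** Simulation under no treatment effect (200,000 runs per scenario; q = 10-30%, mortality 70% vs 10%, 44 or 51 per arm) gives a false-positive rate of 4.4% to 5.9% over all randomizations. Among the 1% to 13% of trials with an imbalance of at least 15 points, it is 14% to 19%.

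**Step 5: quality of life.** Assume a 10-20 point difference between categories and SD 20. The disease-mix part is 15.5% × 10 = 1.6 to 19.0% × 20 = 3.8 points (95% range), against a standard error of 20 × √(2/51) = 4.0. Variance explained is q(1−q)d²/SD²: 0.16 × 100/400 = 4% to 0.24 × 400/400 = 24%. The interval narrows by 1 − √(1 − R²), that is 2% to 13%. This ignores the covariates already in the model, so the gain shrinks to the extent that baseline scores already carry the disease difference.

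**The case against.** The strongest case against is that nothing here is wrong. An unadjusted comparison in a randomized trial is valid, and the secondary results are expressly descriptive. **This stands** and settles what kind of point it is. A reader might infer that disease mix biases the long-term comparisons, or that the ±9 to 11 points come on top of their uncertainty. Neither follows: the test keeps close to its nominal level, and Step 2 shows that the imbalance is inside the standard error. The 14-19% false-positive rate applies only to the minority of trials with a large observed imbalance.

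A reader might also infer that the category is used nowhere else. The text calls it one of the variables for baseline comparability, which does not exclude other uses. Study organization refers to a prespecified statistical analysis plan that is not shown, and a supportive adjusted analysis may be there. **This stands as a caution.** However, the article itself names the covariates and tests for these endpoints, and the category is not among them.

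It would be too strong to say that the quality-of-life analysis ignores disease, because the pre-surgery scores can absorb part of its effect. **This stands.**

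Finally, the gain may be small. Entry on suspected cancer narrows the mix. The article does not say whether the recorded category is the preoperative suspicion or the final histology; if it is the suspicion, nearly everyone may fall in one group. At a 20% share the smaller group has about 10 patients per arm (0.2 × 51), so fine strata would be sparse. **This limits the expected benefit** and argues for two broad groups. It does not argue against naming the factor in advance.

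**Conclusion.** The point holds as a worthwhile improvement in precision, not as an error. The article collects a variable that is plausibly prognostic, states only a baseline-comparability use for it, and fixes 3-year analyses that omit it. For mortality, with 20-40% of patients in a better-prognosis category and a 60-point gap, disease mix accounts for up to about ±9 to 11 points of the arm difference, within a standard error of about 9-10 points. Across the assumed scenarios adjustment removes 6% to 43% of the outcome variance. The case is strongest for mortality and recurrence, the latter because its definition is not limited to confirmed malignancy. It is weaker for quality of life.

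Every size given rests on assumed disease shares and outcome gaps. The operating-time analysis, its sample size and the confirmatory conclusion are unaffected.

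**What to change.** In the analysis plan:

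1. Define the primary-disease category as recorded at baseline, in two broad groups, and state whether it is the preoperative diagnosis.
2. Add it as a factor to the quality-of-life covariance analysis, next to age and the pre-surgery score.
3. Report 3-year mortality and local recurrence stratified by or adjusted for it, for example as a Mantel-Haenszel risk difference, alongside the crude comparison.
4. State that these analyses are done whatever the baseline table shows, and keep that table descriptive.

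The cost is wording and one degree of freedom; no new data are needed. The downside is little gain if nearly all patients fall in one category.

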##### Adverse events and serious adverse events

AEs will be reported to the principal investigator in regular intervals during the course of the study and will be documented in the CRF. It is necessary to note the date, the symptoms, beginning and end, treatment, severity (mild, moderate, severe) and the context of the operation (except those events detected in the endpoints).

SAEs which meet one of the definitions of the secondary endpoints are treated as SAEs regarding their documentation but do not have to be reported to the sponsor (Covidien GmbH, Germany) and principal investigator ([name]. [name], Chairman of the Department of General, Visceral and Transplantation Surgery, University Hospital of Heidelberg) within 24 hours. They will be reported to the principal investigator in regular intervals throughout the study. The surgical trial coordinator will also cross-check the SAEs/AEs of all patients.

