## Background

The procedure was originally described by Alessandro Codivilla in 1898, A.O. Whipple improved it in 1935. The Whipple procedure is the standard method for therapy of cancerous tumours, inflammation and stenosis near the head of the pancreas. In the classic Whipple-procedure (c-Whipple) the head of the pancreas, the duodenum, the regional lymph nodes, the gastric antrum, the gallbladder, and the distal bile duct are removed. The pylorus-preserving-Whipple procedure (pp-Whipple) was established by Traverso and Longmire in 1978. During this procedure the gastric antrum is not removed. In recent years the pp-Whipple procedure is preferred because several studies have shown that the classic Whipple procedure is not superior to the pp-Whipple procedure regarding the oncological outcome or peri- and postoperative complication rates [1-5].

About 300 patients are operated on following the pp-Whipple procedure at the department each year. As the pancreas is fed by many vessels [6], it is necessary to use lots of ligatures, clips and sutures for hemostasis after dissection. This dissection technique is very time-consuming and requires numerous changes of instruments. The use of high-frequency feedback-controlled electrothermal bipolar vessel sealant technology, known as the LigaSure™ Vessel Sealing System (LVSS), is a new alternative for dissection and hemostasis. The bipolar vessel dissection devices require no change of instruments for dissection and hemostasis [7-10]. The current is provided by a special HF-generator and contains a very high capacity with a low voltage. The body's proteins, such as collagen and elastin, are converted so a permanently sealed zone results. As only the tissue between the branches is sealed, lateral thermic tissue damages can be limited to a minimum. Several authors describe a tendency of reduced intraoperative blood loss and transfused blood preservations [11-13]. Other trials show reduced operating time using the LVSS in several surgical procedures, such as thyroid, gynecology, urology and haemorrhoidectomy surgery [9,11,13,14].

Correct dissection in the operation field is very important to avert secondary bleeding or other complications, which might cause re-operation or elevate the patients' morbidity and mortality [15].

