pp-Whipple specific complications	postoperative pancreatic fistula (POPF)	Drain output of any measurable volume of fluid on or after postoperative day 3 with an amylase content greater than 3 times the serum amylase activity. Three different grades of POPF (grades A, B, C) are defined according to the clinical impact on the patient's hospital course [22]
	
	Intraabdominal abscess	Intraabdominal collection of purulent or infected fluids (positiv bacterial culture) requiring radiological (puncture or drainage of purulent fluid) or surgical intervention (re-operation)
	
	anastomotic leakage of choledochojejunostomy	Bilirubin-rich (more than 5000 units) drainage fluid of more than 50 ml per day on or after the 10th postoperative day OR Mentioned in re-operation report
	
	anastomotic leakage of gastrojejunostomy	Radiological findings correlating to gastrojejunostomy insufficiency (e.g. CT with contrast medium withdrawal) OR Mentioned in re-operation report

Further secondary endpoints		Definition

Re-intervention	operational	Reoperation due to any cause

	interventional	Interventional haemostasis or drainages due to any cause

Intraoperative blood loss		Mentioned in operation report

Hospital stay		Time of admission to discharge

Re-hospitalization-rate		Re- hospilization within 30 days after surgery due to any cause

Duration of anesthesia		Mentioned in anesthesia report

Intraoperative material consumption		All materials, which are necessary for surgery

Material costs		Costs, which occurs due to the material consumption during the surgery

Overall costs		Costs include expenditure for personnel and use of operating room as well as for material consumption

Local recurrence of disease		Radiological (ultrasound, CT) findings positive for recurrence of disease

Quality of life		EORTC QLQ-C30, EORTC QLQ PAN26 and special questionnaire of the European Pancreas Center Heidelberg on day 30 (±10days), 90 (±10 days), 180 (±10 days), 1 year (± 1 month), 1,5 years (± 1 month), 2 years (± 1 month), 2,5 years (± 1 month) and 3 years (± 1 month)

Mortality rate		Death to any course until year 3 after operation

Assessment:

1. Perioperative complications of the pp-Whipple procedure will be recorded on the day of operation by an independent study nurse.

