## Study organization

After approval of the protocol by the local ethics committee of the University of Heidelberg, the trial was internationally registered at Germanctr.de (DRKS00000166). All patients scheduled for a pp-Whipple procedure in the Department of General, Visceral and Transplantation Surgery, University Hospital of Heidelberg, will be referred to and screened by members of the Clinical Study Center Surgery (KSC). The results of the screening will be recorded in the screening-log.

Approximately 300 patients per year undergo a pp-Whipple procedure in the Department of General, Visceral and Transplantation Surgery, University Hospital of Heidelberg. The estimated time frame to randomize 102 patients will be approximately 15 months.

The sponsor of the DISSECT trial is Covidien GmbH (Germany).

The independent data management and statistical analysis will be carried out by the Institute of Medical Biometry and Informatics (IMBI) of the University of Heidelberg according to a prespecified Statistical Analysis Plan. It controls the completeness and correctness of the CRF as well as the administration.

The principal investigator has the right to terminate the trial and to remove all trial material from the trial centre at any time in consultation with the Clinical Study Team Leader and the Biostatistician. Reasons that may require a termination of the trial include the following:

• The incidence or severity of adverse events in the trial indicates a potential health hazard caused by the study treatment

• It appears that the patient's enrolment is unsatisfactory with respect to quality or quantity or data recording is severely inaccurate or incomplete

• External evidence that renders the necessity to terminate the trial

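### The exemption of endpoint SAEs from 24-hour reporting has no limit by severity or cause, so it covers perioperative death, re-operation and secondary bleeding, the events most likely to show harm from the dissection technique

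*Protocol article*

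**What the plan says.** Three parts of the Protocol article bear on this.

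- **Reporting rule** (Safety aspects, Adverse events and serious adverse events): events of this kind that match a secondary endpoint definition count as SAEs "regarding their documentation but do not have to be reported to the sponsor". The release is from the 24-hour deadline, and it applies to the principal investigator too. Instead, "They will be reported to the principal investigator in regular intervals throughout the study". The surgical trial coordinator also cross-checks the AEs and SAEs of every patient.
- **Endpoint definitions** (Secondary endpoints, Table 2): mortality is "Death to any course until year 3 after operation", and operative re-intervention is "Reoperation due to any cause". Secondary bleeding is defined by transfusion of more than 2 units of red cells in the first 24 hours or by surgical treatment. Intraoperative bleeding, organ perforation, pancreatic fistula, abscess, anastomotic leakage and readmission within 30 days are also on the list.
- **Termination** (Study organization): the principal investigator may stop the trial at any time, after consulting the team leader and the biostatistician. One listed reason is "The incidence or severity of adverse events in the trial indicates a potential health hazard caused by the study treatment".

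The Background states the harm pathway: "Correct dissection in the operation field is very important to avert secondary bleeding or other complications". It goes on to name re-operation, morbidity and mortality as possible results.

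**The concern.** The exemption is defined only by membership of the endpoint list. It has no limit by severity or by cause. Because two of the endpoints are all-cause (death and re-operation), a fatal haemorrhage after a failed seal falls under the same exemption as a mild fistula that happens to count as serious.

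In a drug trial with a disease-related endpoint, such an exemption usually removes expected events that say little about the treatment. Here the endpoint list is largely a list of surgical complications, and the intervention under test is a way of dissecting and sealing vessels. The exempt events are therefore the informative ones. The person who may stop the trial on safety grounds is formally told of them only through the periodic report. At stake is how quickly a cluster of bleeding, re-operation or death in one arm would reach that person and the sponsor by a documented route.

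**Working it through.** The plan gives no figure for safety reporting, so there is none to reproduce. The check is mainly to set the reporting rule against the endpoint list.

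**Step 1: which serious events are exempt.**

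| Event, if serious | Secondary endpoint in Table 2? | Limited by cause? | 24-hour report required? |
|---|---|---|---|
| Death, up to year 3 | Yes | No | No |
| Re-operation | Yes | No | No |
| Secondary bleeding (transfusion or surgery) | Yes | No | No |
| Severe intraoperative bleeding, perforation, lesion of a solid organ | Yes | No | No |
| Fistula, abscess, anastomotic leakage | Yes | No | No |
| Readmission within 30 days | Yes | No | No |
| Serious event that meets none of these definitions | No | Not applicable | Yes, by implication |

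The last row is an inference. The article does not state the 24-hour rule for other SAEs, but an exemption from it makes sense only if the rule exists.

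**Step 2: compare with the harm pathway.** The Background runs from poor dissection to secondary bleeding and other complications, then to re-operation, morbidity and mortality. Bleeding, re-operation and death are each in an exempt row. What stays on the 24-hour route is mostly the set of events least informative about the technique.

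**Step 3: compare with the termination right.** The safety reason for stopping rests on how often adverse events occur and how severe they are. The holder of that right is one of the two recipients released from the 24-hour report. The two sections do not contradict each other in terms, but the first delays the information on which the second relies.

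**Step 4: what a narrower exemption would cost in reports.** The number randomized is 102, which is 88 + 14 (Number of patients needed). The article gives no rate of early death or re-operation, so I assume 5% to 15%.

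- Low: 102 × 0.05 = 5.1, about 5 reports.
- High: 102 × 0.15 = 15.3, about 15 reports.
- Over the roughly 15 months of recruitment: 5.1 / 15 = 0.34 and 15.3 / 15 = 1.02 per month, so between about one every three months and one a month.

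Bleeding that meets the transfusion definition without re-operation, and device-related SAEs of other kinds, would add somewhat to this. Late deaths are not counted. Mortality runs to year 3 in patients with suspected cancer of the pancreatic head, so including late deaths would raise the number and tell little about dissection.

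**The case against.** The strongest reply is that this is an ordinary design choice. Exempting endpoint events from expedited reporting is common, the endpoint SAEs are still documented as SAEs, and the department has used the device for several years. The principal investigator chairs the single participating department, receives periodic reports, may terminate at any time, and has a coordinator who cross-checks every AE and SAE. Most of this stands. It does not answer why all-cause death and re-operation share the exemption in a trial of a dissection technique. Informal awareness within a department is also not a documented report, and it does not reach the sponsor.

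Three stronger readings are tempting, and the article does not support them.

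- **That the stopping criterion cannot work.** It calls for a cumulative judgement, and the periodic reports and cross-check still feed it. What is removed is a deadline, not the information.
- **That the severity of endpoint events goes unrecorded.** The AE paragraph has a bracket, "except those events detected in the endpoints", but it follows directly on the item about the context of the operation and most naturally limits only that item. The next paragraph keeps full SAE documentation for endpoint events. At most the wording is ambiguous.
- **That the reporting interval is undefined, so that a countable number of patients is operated on before a signal is seen.** A condensed article may leave the interval to the full protocol, and any patient count would rest on an invented interval.

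**Conclusion.** The point holds in a limited form. The article states an exemption with no limit by severity or cause, and its own endpoint definitions bring perioperative death, re-operation and secondary bleeding within it. This delays formal notice of the most informative events to the person who can stop the trial, and to the sponsor. It does not cut off that notice.

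The conclusion rests on stated text and not on an omission, so the full protocol's interval or any monitoring body described there would reduce its weight but not remove it. The only figure, about 5 to 15 extra reports, depends on the assumed 5% to 15% rate of early death or re-operation. It measures the cost of the change, not the harm avoided, for which the article gives no basis. I rate this a cheap safety improvement. It does not affect the validity of the primary comparison.

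**What to change.** Reconcile the reporting rule in Adverse events and serious adverse events with the termination right in Study organization by narrowing the exemption. Keep 24-hour reporting to the principal investigator and the sponsor for:

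- deaths and re-operations in the perioperative period, for example up to the day-30 visit;
- secondary bleeding as defined in Table 2, where it is an SAE;
- any SAE judged related to the device.

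Other expected non-fatal endpoint complications can stay exempt, and late deaths in follow-up can stay on periodic reporting.

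The cost is an amended paragraph and the modest number of extra reports worked out above, handled by the existing study staff and coordinator. Endpoint SAEs will also need a prompt judgement of relation to the device, so that the third item can operate. I would not add comparative tables by arm for the principal investigator. The surgeons are unblinded and the responsible physician enters the operating time in the CRF, so interim comparisons given to the head of the operating department carry a risk of bias that this change does not need to incur.
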